## Abstract

**Background:**

Augmented reality (AR) has benefits and feasibility in emergency medicine, especially in the clinical care of patients, in operating rooms and inpatient facilities, and in the education and training of emergency care providers, but current research on this topic is sparse.

**Objective:**

The primary objective is to evaluate the short-term and long-term effectiveness of the use of AR in the treatment of patients with anaphylactic shock. The secondary objectives are to evaluate the safety in the treatment of patients with anaphylactic shock, evaluate the short-term and long-term effectiveness of stress management in this process, and determine the experiences and attitudes towards the use of AR in education.

**Methods:**

The study will be conducted in 3 phases. In the first phase, we will develop and test the scenario for simulation of anaphylactic shock and the evaluation scale for assessing the effect of the intervention. In the second phase, a single-blinded, randomized controlled trial will be conducted. In the third phase, the use of AR in teaching the management of anaphylactic shock using focus groups will be evaluated qualitatively. All participants will participate in a 1-day training program consisting of a lecture on emergency care and anaphylactic shock as well as exercises in manual dexterity (aspiration, airway management, alternative airway management, artificial respiration, chest compressions, safe defibrillation, oxygen application, use of medication during emergency care). The test group will also focus on education about anaphylactic shock in AR (the intervention). 
The main outcome will be the evaluation of the participants' performance in coping with a simulated scenario of anaphylactic shock using a high-fidelity simulator (simulator with high levels of realism) and a standardized patient in an educational and clinical environment. The study will be conducted with primary care physicians.

**Results:**

A scenario for the simulation with a high-fidelity simulator and standardized patient has already been developed. For the time being, we are developing an evaluation scale and starting to recruit participants. We plan to complete the recruitment of participants by the end of December 2020, start the randomized controlled trial in January 2021, and finish 1 year later. The first results are expected to be submitted for publication in 2021.

**Conclusions:**

This will be the first study to evaluate the effectiveness of the use of AR in medical teaching. Specifically, it will be based on a clinical case of anaphylactic shock at the primary care level. With our study, we also want to evaluate the translation of these educational results into clinical practice and assess their long-term impact.

**Trial Registration:**

ISRCTN Registry ISRCTN58047410; http://www.isrctn.com/ISRCTN58047410

**International Registered Report Identifier (IRRID):**

PRR1-10.2196/22460

## Introduction

Augmented reality (AR) is a technology that enhances the user's reality with the help of digital information [1]. It maintains the user's connections with the real world and synthesizes the virtual with the real. It typically involves a headset through which one can view a physical reality that has been expanded or supplemented by computer-generated sensory inputs such as sound, video, and graphics [2]. AR differs significantly from virtual reality (VR), as the latter is completely immersive (ie, the real [external] world is completely blocked by the headsets) [2].

In the health care sector, AR is used in medical training [3-5], for surgical interventions [6,7], in nursing [8], in rehabilitation [1], in emergency medicine [2,9], and as a therapeutic aid [10]. In health education, it is used in a wide range of subjects (eg, surgery, forensic medicine, anatomy, clinical life support, cardiology) [4]. Educators use various devices, such as smart glasses, tablets, and smart watches [8]. Systematic reviews from the field of AR in medical education report that the subject is increasingly researched but still in the early stages. Studies have mainly focused on the development, usability, and first implementation of AR for learning. Perhaps the value of this teaching method lies in its motivational effect, the training of psychomotor skills, and the ability to make the invisible visible [5]. However, designed AR applications lack an explicit pedagogical framework [4], and there is no evidence that these applications are able to transmit information to the user [3]. There are also no clinical studies that support the effectiveness of the AR technologies used [1].

In emergency medicine, AR has benefits and feasibility in the clinical care of patients, in operating rooms and inpatient facilities, and in the education and training of emergency care providers, but current research on this topic is scarce [2]. Previous studies have shown that AR can enable reflection through experience [11] and can be useful in procedural learning [2]. It also appears that AR adds an extra level of realism to simulation learning, which improves learner self-confidence and teamwork [2].

Emergency management is an integral part of primary care. As a primary care provider, primary care workers can be confronted with any type of emergency that requires updated knowledge, communication and manual skills, trained personnel, appropriate equipment and practice organization, and necessary medication. The wide range of symptoms and the rarity of situations make it difficult for primary care staff to keep up to date and be competent in life support [12]. The use of new training methods, such as classroom simulations with 3-dimensional (3D), highly realistic simulators [13] or in situ simulations, can provide comprehensive training in handling medical emergencies and identifying potentially dangerous medical situations that are not part of the daily work of primary care physicians and other health care workers [14].

Despite the growing body of evidence that AR is effective in medical education, some studies failed to confirm this, reporting no significant impact of the use of AR on learning and no differences according to device used (mobile or other) [15].

There are also several disadvantages of AR use for medical education that could be important, such as the possibility of deteriorating human connections; technical problems, which could affect the learning process; lack of privacy during learning; and questionable cost benefit.

The primary objective of this study is to evaluate the short-term and long-term effectiveness of the use of AR in the management of patients with anaphylactic shock. The secondary objectives are to assess the safety in the treatment of patients with anaphylactic shock, evaluate the short-term and long-term effectiveness of stress management in this process, and determine the experiences and viewpoints of participants regarding the use of AR in education.

## Methods

### Study Design and Settings

This is a mixed-methods study, incorporating quantitative and qualitative methodology and operating under a pragmatism paradigm.

The study will be conducted in 3 phases. In the first phase, we will develop and test the scenario for simulation of anaphylactic shock and the evaluation scale for assessing the effect of the intervention. In the second phase, a single-blinded, randomized controlled trial (RCT) will be conducted. In the third phase, a qualitative methodology with focus groups will be used to assess the attitudes and experience regarding AR use in participants.

The study will be conducted in a primary health care setting, partly in a classroom and partly in a clinical setting. The Slovenian Ethics Committee (No. 0120-67/2020/6) approved the protocol.

### Participants and Recruitment

#### Phase One

Up to 10 experts from the fields of family and general medicine, emergency medicine***,*** and internal medicine will participate in the development of the scenario for the simulation with a high-fidelity simulator and for AR as well as the evaluation scale for assessing the effect of the intervention.

#### Phase Two

Family medicine physicians will participate in the study. We will send an invitation to all family physicians in Slovenia via the register of family medicine physicians at the Slovenian Medical Chamber. We plan to recruit 150 participants. They will be randomly divided into test and control groups. Inclusion criteria will be a signed informed consent and willingness to participate. Exclusion criteria will be physical inability to participate in activities, previously experienced side effects of using AR, and heart disease.

#### Phase Three

For the focus groups, participants from the test group will participate. According to the guidance in previously reported studies, we expect to include a minimum of 4 participants and a maximum of 12 participants per group [16-19]. Qualitative data collection will be continued until data saturation is achieved. According to Guest et al [20], more than 80% of all themes are discovered by using 2-3 focus groups, and 90% are found by using 3-6 focus groups. For this reason, we anticipate having 3-6 focus groups; however, if the point of saturation is achieved sooner, fewer focus groups will be performed. If possible, focus groups will be stratified by work experiences (<10 years’ experience, 10-20 years’ experience, >20 years’ experience). We feel that family physicians will be more open when in a group with physicians who have similar experience.

### Procedures and Data Collection

#### Phase One

The simulation scenario (the simulation is presented with a high-fidelity simulator in a learning and clinical environment and for AR) is being developed by the researchers on the basis of the 2015 European Resuscitation Council guidelines and 2015 European Academy for Allergology and Clinical Immunology guidelines. The experts will validate the scenario and thus ensure its validity.

An evaluation scale will be developed to assess the impact of the intervention. The evaluation criteria will be developed based on the 2015 European Resuscitation Council guidelines and 2015 European Academy for Allergology and Clinical Immunology guidelines. These criteria are reviewed by the experts using a 2-step Delphi methodology. In the first step, the usefulness of items for assessment are assessed using grades 1 to 7, where 1 means that the criterion is not useful at all and 7 means completely useful. To be included in the evaluation scale, each criterion has to be given an average score of ≥5 points. In the second stage, the rating scale is re-evaluated by experts who express their agreement with the rating scale. We will aim for a consensus rate of 90%. Through this process, we will obtain the final version of the rating scale [21].

#### Phase Two

The flow of the study is presented in Figure 1. The study is expected to last for 1 year. Before the intervention, we will assess the baseline characteristics of the participants. All participants will complete the questionnaire on demographic and other data (see Measures). They will also complete the Folkman-Lazarus Ways of Coping Questionnaire (WCQ; please see Measures for more information) [22]. The baseline knowledge, skills, and competencies of the participants regarding the management of a patient with anaphylactic shock will be assessed through a simulation based on the developed scenario using a high-fidelity simulator in a learning environment (a classroom). The participants will perform the simulation in a group of 3; the other 2 members of the group will be educated trainers. They will follow the leadership of the individual participant and not engage in actions until instructed by the participant. The simulation will be video recorded. The recordings will be independently assessed by 3 experts that will not be aware of the participant’s group allocation (blinded), based on the developed evaluation scale. They will harmonize their assessment and produce a single result. This will be in the form of a numeric outcome (primary outcome result) and in a binary form (successful/not successful).

**Figure 1 figure1:**
[figure not shown]
Schematic presentation of the randomized controlled trial in phase two of the study. WCQ: Ways of Coping Questionnaire.

After the intervention (see Intervention), the participants will once again perform the simulation with a high-fidelity simulator and complete the WCQ, which will be followed by a debriefing. We will use a structured tool for debriefing called TALK (Target, Analysis, Learning Points, Key Actions), which is designed to guide structured team self-debriefing after any learning event in clinical environments. It promotes a supportive culture of learning and patient safety [23]. The simulations will be again video recorded, and the recordings will be assessed by experts as already described.

Both groups will be assessed again at 1 month and 1 year after the intervention, using the WCQ scale and simulation. This time, the simulation will be performed in the participant’s workplace and with a standardized patient, followed by a debriefing. The scenario of the simulation will be the same as before. Again, simulations will be video recorded; experts, as already described, will assess the recordings.

The short-term effect will be measured using performance immediately and 1 month after the intervention, while the long-term effect will be measured 1 year after the intervention, which will also be our primary time point.

#### Phase Three

Within 1 month after the intervention, the focus groups consisting of the test group members will be conducted according to qualitative methodology principles. The focus groups will be led by an experienced family physician who has extensive experience in conducting qualitative research and a family physician who will be observing and recording. Participants will be told that the focus groups' primary goal is to explore the experiences, beliefs, and views, providing a comprehensive understanding of the knowledge that participants had with AR in education.

Each focus group will last approximately an hour and will be audio-recorded. Participants will sign an agreement to be recorded. The recordings will be archived for 1 year, then destroyed. Participants will be seated at a round table so they can see each other. Before the group starts, each participant will be provided with a copy of the rules to respect other's opinions, listen to others, and speak in turn. Audio-recordings will be transcribed verbatim.

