### Intervention

All participants will participate in a 1-day training program consisting of a lecture on emergency care and anaphylactic shock as well as exercises in manual dexterity (aspiration, airway management, alternative airway management, artificial respiration, chest compressions, safe defibrillation, oxygen application, use of medication during emergency care). The test group will receive education on anaphylactic shock in AR. Training with AR is a scenario for the management of a patient with anaphylactic shock. When the head-mounted display is put on, a woman with symptoms of anaphylactic shock that gradually worsen can be seen. Her breathing becomes difficult, an urticarial rash appears, and she says she does not feel well and cannot breathe. When she is asked questions, she answers. The participant must then take the necessary steps to treat this patient correctly; otherwise, the augmented patient will die.

AR intervention represents a combination of standardized and evaluated medical procedures corresponding to a specific medical event (in our case, anaphylactic shock) and digital support id software. Development of an AR intervention consists of (1) defining a medical event, (2) analysis and documentation of crucial parameters (eg, patient type, symptoms, procedures, measurements, medication, equipment involved [eg, monitor, pulse oximeter], decision tree, execution process, and time perspective), (3) defining targeted users or user groups, (4) creation of the use case scenario, (5) defining the expected (un)wanted outcome in the form of standardized results (points achieved, success rate in percentages), (6) software development (environment creation including all 3D assets, animations, sounds, and user interactions), and (7) integration of all elements described into the most believable realistic, holistic experience producing adequate levels of stress in regards to the potential real case scenario.
The AR intervention was developed by a group of medical experts (doctor, nurse, and instructor) and information technology experts (user experience engineers, 3D artists, designers, AR developers, and product specialists).
The AR intervention will be delivered in the form of software as a service, meaning an application supporting available devices for distributing AR content. Add-ons to the application will be web space for user management and tracking of participant success (pass rate).

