## Discussion

### Expected Results

This will be the first study to evaluate the effect of using AR for teaching in an urgent primary health care situation. The main outcome of this study will be the short-term and long-term effectiveness of the use of AR in the training of primary care physicians. We expect that the participants who are trained with AR in addition to the standard training will achieve better results in the treatment of a patient with anaphylactic shock in the simulation compared to other participants.

Several systematic, scoping, and integrative reviews on the use of AR in medical education showed that, while AR technology is growing at a rapid rate, the current quality and breadth of AR research in medical training are insufficient to recommend its adoption into educational curricula [2-4,29]. Existing studies mainly focus on the evaluation of prototypes instead of long-term studies. There is a lack of evidence for the implementation of AR in medical education [8], including training in emergency care [9], even though some studies demonstrated its effectiveness [2,11]. Therefore, we expect that our study will fill the gap on the effectiveness of AR in medical training and provide new insights into its short-term and long-term effects.

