There are some drawbacks of simulation in health care. Simulation relies on space, time, equipment, and skilled human resources. Setting up and running the simulation can be expensive [30]. The simulation center where the study will be conducted is an already established and active center with many simulation trainings conducted over previous years [14]. Therefore, we are certain that these drawbacks will be handled appropriately. Another problematic issue in simulation might be the need for an adaptation period for students to perform the simulation. It is mainly during the second simulation that a student will really start to be able to adapt and treat the patient simulator more realistically [30]. We are aware that this could affect the results of our study, but given the fact that all participants will have the same conditions, we think that this drawback will also be handled appropriately.

In education at all levels and in all fields, studies usually focus on short-term results, assessing the outcome during or immediately after the time when the education took place. Unfortunately, it is true that mastery demonstrated during or immediately after learning can easily be lost in the weeks and months that follow without continued practice [6]. Therefore, in this study, we have chosen to evaluate the short-term and long-term effects by assessing performance immediately after the intervention and 1 month after, given that short-term performance is a good predictor of performance over longer periods of time, and 1 year after the intervention (long-term effect). The long-term preservation of knowledge is the most important, as it is an indicator of permanent memory.

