### Conclusions

This will be the first study to evaluate the effectiveness of the use of AR in teaching medicine based on a clinical case of anaphylactic shock at the primary care level. With this study, we will evaluate the implementation of AR-related educational results in clinical practice. We will also be able to assess their long-term impact. This study will also serve as a basis for other research in the field of training with AR.

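### Test-arm-only focus groups come before the 1-year primary assessment and may come before the 1-month one, and the claim that all participants share the same conditions does not hold for simulated-case exposure

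*Protocol article*

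**What the plan says.** **Training.** The Intervention section gives both arms the same day: "All participants will participate in a 1-day training program consisting of a lecture on emergency care and anaphylactic shock", together with manual-skills exercises. One component is then reserved for one arm: "The test group will receive education on anaphylactic shock in AR". Its content is described so: "Training with AR is a scenario for the management of a patient with anaphylactic shock". No activity is described for controls in its place. Expected Results gives the hypothesis as an add-on: "participants who are trained with AR in addition to the standard training will achieve better results".

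**Assessments.** Under Procedures and Data Collection, Phase Two, both arms are tested by simulation at baseline, after the intervention, at 1 month and at 1 year, with the scenario kept the same. The simulations after the intervention are followed by a debriefing in both arms. One year is the primary time point.

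**Focus groups.** Only test-arm members are eligible. On timing: "Within 1 month after the intervention, the focus groups consisting of the test group members will be conducted". On number: "we anticipate having 3-6 focus groups", each with 4 to 12 people, and fewer groups if saturation comes sooner. Each lasts about an hour.

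**Adaptation to simulation.** The Methodology part of the Discussion accepts that learners adapt mainly at their second simulation and that this could affect the results. It then sets the matter aside: "given the fact that all participants will have the same conditions, we think that this drawback will also be handled appropriately".

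**Conclusion drawn.** The Conclusions section says: "This will be the first study to evaluate the effectiveness of the use of AR in teaching medicine", based on an anaphylactic shock case in primary care. The Abstract's conclusion is similar.

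**The concern.** There are two separate differences between the arms.

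The first is a by-product of the study's own schedule. An hour of peer discussion is given to one arm between the intervention and the assessments. The Methodology text says the focus groups will also judge how well the AR application covers the medical content, so the talk need not stay on opinions about the technology. The Limitations section accepts that training on the subject between assessments could change performance, but it does not mention this exposure, which the trial itself creates in one arm only.

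The second is that the stated reason for disregarding adaptation to simulation is not accurate as written. The test arm works through one more simulated case than the controls.

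At stake is the interpretation of a positive result. Part of a test-arm advantage could come from an extra rehearsal or, for attendees, from the discussion. A reader could take the conclusions as evidence about AR as a teaching medium, which this comparison cannot isolate.

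**Working it through.** **1. The plan's own figure.** Inputs from Power Calculation: difference 10 points, SD 20, two-sided alpha 0.05, power 80%.
- Normal approximation: 2 × (1.960 + 0.842)² × 20² / 10² = 62.8, so 63 per arm.
- Exact two-sample t test with d = 10/20 = 0.5: 63.77, so 64 per arm and 128 in total, power 80.1%. This reproduces the stated 128.
- Recruiting 150 allows for 1 − 128/150 = 14.7% dropout.

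Nothing in this point changes the sample size.

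**2. Timing of the focus groups.** The window runs from the intervention to 1 month. The assessments are immediate, at 1 month and at 1 year. The window therefore closes at about the 1-month assessment and about 11 months before the primary one. A member may attend before the 1-month simulation, and every member attends before the 1-year simulation.

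**3. How many could attend.** Assumption: equal allocation, so 150/2 = 75 in the test arm.
- Lower planned figure: 3 × 4 = 12, and 12/75 = 16%.
- Upper planned figure: 6 × 12 = 72, and 72/75 = 96%.
- Controls: 0.

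The lower figure is not a floor, since early saturation may stop the groups sooner. The upper figure needs the maximum of both ranges. These are attendance figures, not estimates of bias.

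**4. Simulated anaphylaxis cases met before each test.**

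| Before the test at | Control | Test arm |
|---|---|---|
| Immediately after intervention | 1 (baseline) | 2 (baseline, AR) |
| 1 month | 2 (baseline, immediate) | 3 (those two, AR) |
| 1 year (primary) | 3 (baseline, immediate, 1 month) | 4 (those three, AR) |

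The difference is one case throughout. The immediate test is thus the second simulated case for a control and the third for a test-arm participant.

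**5. What an unrelated shift would do (illustration only).** The documents give no size for a practice or discussion effect, so the shifts below are assumed. Suppose AR as a medium has no effect, and something else raises the test-arm mean. With 64 per arm and SD 20, the standard error is 20 × √(2/64) = 3.54 points, and the planned t test is significant with these probabilities:

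| Assumed shift in arm mean (points) | Probability of p < .05 |
|---|---|
| 0 | 5.0% |
| 1 | 5.9% |
| 2 | 8.7% |
| 3 | 13.4% |
| 5 | 28.9% |

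For the focus groups alone, the shift in the arm mean is the gain per attendee times the share attending. An assumed gain of 3 points per attendee gives 0.16 × 3 = 0.48 to 0.96 × 3 = 2.88 points, so a probability between 5% and just under 13.4%. A gain that persists for 11 months after one hour of discussion may well be smaller.

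**The case against.** The AR rehearsal is the intervention, not a confounder. The Abstract and Expected Results already describe AR on top of the standard training, and such a comparison is legitimate in a study that declares a pragmatic stance. Asking for a matched non-AR rehearsal in the control arm is a preference for a different question. This stands.

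A reader might infer that only the test arm rehearses the tested emergency, or that no difference could be credited to AR at all. The document supports neither. Both arms run the same scenario at every assessment, and the effect of adding the AR session remains estimable.

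The focus groups are meant to explore experiences and views about AR in education, and both arms receive debriefing about the clinical case. Nothing in the document shows that an hour of such discussion moves a guideline-compliance score. This too stands in large part. It limits the likely size of the effect but does not remove the imbalance, because the groups are also to judge content coverage and controls have no counterpart.

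The equal-conditions sentence can be read as referring to the assessment simulations, for which it is correct. Adaptation is said to come mainly at the second simulation, which controls have reached by the immediate test, and both arms are past that stage by 1 year, when a standardized patient is used. The sentence is still offered as a reply to a practice effect, and total practice is not equal.

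**Conclusion.** The point holds in limited form.

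- The focus groups add a one-arm exposure before the primary assessment and possibly before the 1-month one. By the planned numbers it reaches 16% to 96% of the test arm, assuming 75 per arm. Its effect on scores is unknown and probably small.
- The equal-conditions statement is wrong for total simulated-case exposure, which differs by one case: 2 against 1 before the immediate test and 4 against 3 before the 1-year test.
- The trial can estimate the effect of adding an AR session to the standard day, with focus groups bundled in for those who attend. It cannot separate AR as a medium from one more practice case. The probabilities in the working rest on assumed shifts and show sensitivity, not expected bias.

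This calls for a scheduling change and clearer wording. It does not invalidate the design or the sample size.

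**What to change.** 1. Change the Phase Three timing so that each focus group meets only after all its members have completed the 1-month simulation. This removes the exposure from both short-term results. The cost is slightly later recall of the AR session.
2. Record who attends, and add a sensitivity analysis of the 1-year result that takes attendance into account. Attendance is not randomized, so this analysis is supportive only. It will say little if nearly everyone attends: with 72 of 75 attending, only 3 members are unexposed. Moving the groups past 1 year would remove the exposure completely, but it trades directly against recall and is not required.
3. Mention the test-arm-only focus groups in Limitations.
4. Reword the Methodology sentence so that equal conditions refers to the assessment simulations only, and say that the test arm has one additional simulated case.
5. Word the conclusions in the Abstract and in the Conclusions section as the comparison already given in Expected Results: the standard training day plus an AR session against the standard day alone. The cost is a narrower claim about AR.

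None of these changes affects the outcomes, the randomization or the 150 participants planned.
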